### 9.3.1 Adverse Event Definitions

**Headache:** a pain located in the head, over the eyes, at the temples, or at the base of the skull lasting more than 30 minutes

**Nausea:** discomfort in the stomach with an urge to vomit

**Malaise:** generalized feeling of being unwell

**Myalgia:** pain in the muscles, in one or more muscle groups

**Arthralgia:** pain in a joint, in one or more joints

**Urticaria:** Hives; a raised, red, itchy skin rash containing wheals

**Table 3 Solicited Adverse Events**

| Systemic adverse events | Laboratory adverse events | Local reactogenicity |
|-------------------------|---------------------------|----------------------|
| Fever                   | Hemoglobin                | Injection pain       |
| Headache                | WBC                       | Injection erythema   |
| Nausea                  | ANC                       | Injection swelling   |
| Malaise                 | ALT                       | Injection induration |
| Myalgia                 | Platelet count            | Injection pruritus   |
| Arthralgia              | Creatinine                |                      |
| Urticaria               |                           |                      |

### 9.3.2 Determination of Severity

Severity of AEs will be assessed by the investigator as described in [Appendix C](#). AEs not included in the Appendixes will be graded for severity using the followings definitions:

- Grade 1 (Mild): No interference with activity, may use 1 dose of an over the counter medication
- Grade 2 (Moderate): Repeated use of non-narcotic pain reliever > 24 hours or some interference with activity
- Grade 3 (Severe): Activities of daily living limited to <50% of baseline, medical evaluation/therapy required

|                             |                                                                                                                                      |
|-----------------------------|--------------------------------------------------------------------------------------------------------------------------------------|
| Grade 4 (Life-threatening): | Extreme limitation in activity, significant assistance required; immediate medical intervention or therapy required to prevent death |
| Grade 5:                    | Death                                                                                                                                |

### 9.3.3 Association with Receipt of the Study Vaccine

All AEs will be assessed for relationship to the study vaccine using the following definition:

|                     |                                                                                                                                                                                                                                                                    |
|---------------------|--------------------------------------------------------------------------------------------------------------------------------------------------------------------------------------------------------------------------------------------------------------------|
| Definitely:  | Clear-cut temporal association, and no other possible cause.                                                                                                                                                                                                       |
| Probably:    | Clear-cut temporal association and a potential alternative cause is not apparent.                                                                                                                                                                                  |
| Possibly:    | Less clear temporal association; other causes also possible.                                                                                                                                                                                                       |
| Unlikely:    | Temporal association between the AE and the vaccine or the nature of the event is such that the vaccine is not likely to have had any reasonable association with the observed illness/event (cause and effect relationship improbable but not impossible). |
| Not Related: | The AE is completely independent of vaccine administration; and/or evidence exists that the event is definitely related to another cause.                                                                                                                          |

The degree of certainty with which an AE can be attributed to administration of the study vaccine will be determined by how well the event can be understood in terms of one or more of the following:

1. The event being temporally related with vaccination or reproduced on re-vaccination
2. A reaction of similar nature having previously been observed with this type of vaccine and/or formulation
3. The event having been reported in the literature for similar types of vaccines
4. Whether or not there is another identifiable cause

All local (injection-site) reactions will be considered causally related to vaccination.

Reports will further classify AEs as follows: Related (all AEs that are assessed as definitely, probably, or possibly related) and Unrelated (all AEs assessed as unlikely or definitely not related), as per [Table 4](#) below. When reporting to regulatory authorities and IRBs is needed, AE relationship will be determined per [Table 4](#).

**Table 4 Assessment of Relationship**

| Related    |          |          | Not related |             |
|------------|----------|----------|-------------|-------------|
| Definitely | Probably | Possibly | Unlikely    | Not related |

## 9.4 Reporting

#### **9.4.1 Reporting to IND Sponsor**

##### **SERIOUS ADVERSE EVENTS**

SAEs will also be reported on the SAE/Unanticipated Problems Report Form and sent to the Sponsor Clinical Safety Office (CSO) by fax or e-mail attachment. All SAEs will be reported within 1 business day after the clinical site becomes aware of the event.

##### **UNANTICIPATED PROBLEMS**

Unanticipated Problems that are AEs will also be reported on the SAE/Unanticipated Problems Report Form and sent to the Sponsor Clinical Safety Office (CSO) by fax or e-mail attachment no later than 14 calendar days of PI awareness of the event. Unanticipated Problems that are not AEs will not be reported to the Sponsor CSO.

Unanticipated AEs will also be reported to the regulatory authorities and IRBs per relevant FDA and IRB guidelines. When an unanticipated AE occurs, the relationship to study product will be assessed per [Table 4](#) and reported accordingly.

#### **Pregnancy**

Pregnancy itself is not an AE. However, pertinent obstetrical information for all pregnancies will be reported to the CSO via fax or email within 3 business days from Investigator awareness of the pregnancy.

Pregnancy outcome data (e.g., delivery outcome, spontaneous, or elective termination of the pregnancy) will be reported to the CSO within 3 business days of the site's awareness of the outcome on a protocol-specified form.

In the event of pregnancy the following steps will be taken:

- Withdraw from the study but continue in follow up for safety
- Report to Western and NIAID IRBs as an unanticipated problem
- Advise research participant to notify the obstetrician of study vaccine exposure

#### **SPONSOR'S REPORTING RESPONSIBILITIES**

Serious, unexpected, suspected adverse reactions (SUSARs) as defined in 21 CFR 312.32 will be reported to FDA and all participating Investigators as IND Safety Reports. The sponsor will also submit a brief report of the progress of the investigation to the FDA on an annual basis as defined in 21 CFR 312.33.

#### **9.4.2 Reporting to the IRBs**

Reporting requirements to the NIAID Institutional Review Board (IRB) for this protocol are as follows:

##### **Expedited reporting:**

Unanticipated problems that are either AEs or non-AEs (as defined above) and protocol violations will be reported within 7 calendar days of investigator awareness. SAEs that are possibly, probably, or definitely related to the research will be reported within 7 calendar days of investigator awareness, regardless of expectedness.

##### **Annual reporting:**

The following items will be reported to the NIAID IRB in summary at the time of Continuing Review:

- All unanticipated problems
- All protocol deviations which, in the opinion of the investigator, will be reported
- All SAEs (related and unrelated, and expected and unexpected).

All SAEs, unanticipated problems, AEs, and protocol violations and deviations will be reported to Western Institutional Review Board (WIRB) as per WIRB guidelines, below:

- **WIRB Guidelines:**

WIRB [contact], [contact]

<http://www.wirb.com/> for updated reporting guidelines

Reports for continuing review to WIRB will be submitted by the investigators per WIRB guidelines. WIRB is the site IRB and as such is the IRB of record for this study.

#### **9.4.3 Reporting to Malaria Vaccine Initiative**

All SAEs will be reported to Malaria Vaccine Initiative (MVI) within 24 hours of investigator awareness. Unanticipated problems and AEs will be reported to MVI at the same time they are reported to WIRB.

MVI contact:

[name]

PATH Malaria Vaccine Initiative

[name]

Direct [contact]

[contact]

[contact]

Phase 1 Study of Pfs25-EPA/Alhydrogel®

Version 6.0

9 January 2013

Email: [[contact]](mailto:[contact])

#### **9.4.4 Reporting to the Safety Monitoring Committee**

SAEs reported to the Regulatory Compliance and Human Subjects Protection Branch (RCHSPB) CSO will be reported to the Safety Monitoring Committee (SMC) Executive Secretary by email or fax according to the RCHSPB SMC Policy. Should halting rules be met the SMC will be notified and a safety review will be scheduled. All AEs will be summarized and forwarded to the CSO Executive Secretary for distribution to the SMC prior to the review. The AE's relationship to study product for this purpose will be categorized according to [Table 4](#).

#### **9.5 Halting Rules**

The PI will closely monitor study data as they become available and will make determinations regarding the presence and grading of AEs. The AEs will be evaluated with regard to the known complications associated with administration of vaccine components. If a dose of vaccine is considered unacceptably reactogenic (as described in the following criteria), the study will be halted. No new enrollments and no further vaccinations will be administered by the Investigators until reviewed by the SMC and study IND Sponsor. A report of SMC recommendations will be submitted to the IRBs. The following criteria will be used to define unacceptable reactogenicity of the malaria vaccine (AEs that are possibly, probably, or definitely related to the vaccine will be considered "Related" as per [Table 4](#) and will be summarized as such):

1. One or more subjects experience an SAE as defined in [Section 9.1](#) of this protocol that is determined to be possibly, probably, or definitely related to the vaccine, **or**
2. One or more subjects experience a hypersensitivity reaction that is probably or definitely related to the vaccine, **or**
3. Any severe clinical illness occurs that is not explained by a diagnosis that is unrelated to vaccination, **or**
4. Two or more subjects in any dose cohort experience any Grade 2 or higher laboratory abnormality (see [Appendix C](#)), or Grade 3 systemic AE that is determined to be possibly, probably, or definitely related to the vaccine as defined in this protocol, **or**
5. One or more subjects experience erythema nodosum.
6. Two or more volunteers in a single dose cohort experience Grade 3 or higher injection site induration or any abscess formation.

The IRBs, the NIAID, the FDA, or other government agencies may discontinue the study at any time. Subsequent review of serious, unexpected, and related AEs by the SMC or IRB, the IND sponsor, the FDA, and other regulatory authorities may also result in suspension of further administration of vaccine at the clinical site. The FDA, other regulatory authorities, and the study sponsor(s) retain the authority to suspend additional enrollment and administration of vaccine for the entire study as applicable.

## **10 Clinical Monitoring**

### **10.1 Site Monitoring Plan**

RCHSPB will provide oversight and monitor the compliance of this trial. Monitors under contract to the NIAID/RCHSPB will visit the clinical site to monitor all aspects of the trial in accordance with appropriate regulations. The objectives of a monitoring visit will be:

1. to verify the prompt reporting of all data points, including SAEs
2. to check the availability of signed informed consent documents and documentation of the ICF process for each monitored subject
3. to compare individual subject's records (e.g. CRFs, electronic data, CRIMSON pulls) to the source documents (supporting data, laboratory specimen records, clinical notes)
4. to ensure the investigators are in compliance with the protocol, and accuracy and completeness of records

The monitors will also inspect the clinical site's regulatory files to ensure that applicable regulatory requirements (FDA, Office for Human Research Protections [OHRP]) and guidelines (ICH) are being obeyed. During the monitoring visits, the PI and/or designated study staff will be available to discuss the study. The site PI will provide direct access and allow the study monitors, LMIV, and regulatory authorities to access all study-related documents.

Prior to the start of the study, the PIs will be informed of the frequency of the monitoring visits and will be given reasonable notification prior to each visit.

Quality control procedures will be implemented beginning with the data entry system, and data quality control checks that will be run on the database will be generated. Any missing data or data anomalies will be communicated to the site for clarification/resolution.

MVI will have the right to audit the site. During the audit the PI and/or designated study staff will be available to discuss the study. The site PI will provide direct access and allow the MVI representative access to all study-related documents.

### **10.2 Safety Monitoring Plan**

#### **10.2.1 Safety Monitoring Committee (SMC)**

An independent Safety Monitoring Committee (SMC) will be formed in accordance with RCHSPB guidelines. The SMC will review the study protocol and safety monitoring plan prior to enrollment and will review safety data should halting rules be met, or at the Investigators' discretion. Written summaries of all SMC meetings and recommendations will be submitted to the IRBs as part of annual continuing review. If halting rules are met or clinical events affecting risk occur, meeting minutes and recommendations will be sent to the NIAID IRB as an informational item. Otherwise such reports will be submitted as part of the annual continuing review.

## 11 Statistical Considerations

### 11.1 Description of Statistical Methods

This study, like other Phase 1 studies, is exploratory rather than confirmatory; its purpose is to estimate AE rates and patterns of immune responses rather than to test formal statistical hypotheses. Estimates will be presented with their 95% confidence intervals. Descriptive approaches will be used to meet the protocol objectives, as well as formal statistical tests as outlined below. Results will be presented in tabular format, as well as graphically where appropriate.

### 11.2 Primary Objective

The primary objective of this study is to assess safety and reactogenicity of Pfs25-EPA/Alhydrogel® in malaria-naïve US adults.

- a. The frequency of systemic and local AEs will be summarized.
- b. A line listing of each clinical and laboratory AE classified as local, solicited, or other will be displayed in tables stratified by vaccine allocation.
- c. AEs will be summarized by severity and relationship to vaccine (according to [Table 4](#)).
- d. The proportion of subjects with at least 1 AE will be compared by vaccine schedule and/or dose group, and tests performed to assess whether these groups differ with respect to these proportions. To see if there is a difference in AEs between the initial vaccination and the subsequent vaccinations, a Wilcoxon signed rank test will be performed, where the response for each subject is the difference between the numbers of AEs in the 2 weeks following each vaccination.
- e. SAEs occurring within the study period will be listed by relationship to vaccine.

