## Précis

A vaccine to interrupt malaria transmission would be a valuable tool for local elimination or eradication of this disease. Pfs25, a surface antigen of ookinetes in the mosquito stage of *P. falciparum*, is a lead candidate for a malaria transmission blocking vaccine. Recombinant Pfs25 has been conjugated to *Pseudomonas aeruginosa* ExoProtein A (EPA), and adjuvanted with Alhydrogel®. This open label, dose escalating Phase 1 study in malaria naïve adults, conducted at Johns Hopkins Bloomberg School of Public Health Center for Immunization Research (CIR) in Baltimore, Maryland, will determine initial safety and immunogenicity of the vaccine given on a 2 dose and 3 dose schedule. Thirty (30) volunteers will be enrolled, with 5 receiving the lowest dose (8 µg of conjugated Pfs25), 5 receiving the middle dose (16 µg of conjugated Pfs25), and 20 receiving the high dose (47 µg of conjugated Pfs25). The low dose groups will receive 2 doses of vaccine and the high dose group will receive 4 doses of vaccine, on a 0, 2 month (low dose) or 0, 2, 4 and 10 month (high dose) vaccination schedule. In addition, extraordinary responders to the low dose of vaccine (as measured by antibody level) will be offered a booster dose at 10 months. Volunteers will be followed for 12 months following the last vaccination. Safety outcomes will be local and systemic adverse events (AEs). Immunogenicity outcomes will be antibody responses as measured by ELISA, transmission blocking in a standard membrane feeding assay, and B and T cell responses.

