**Table 1 Phase 1 Study of Pfs25-EPA Conjugates in US Healthy Adults**

| Group | N  | Vaccine                                 | Schedule (month)  |
|-------|----|-----------------------------------------|-------------------|
| 1a    | 5  | 8 µg Pfs25-EPA/Alhydrogel ®  | 0, 2, optional 10 |
| 1b    | 5  | 16 µg Pfs25-EPA/Alhydrogel ® | 0, 2, optional 10 |
| 2     | 20 | 47 µg Pfs25-EPA/Alhydrogel ® | 0, 2, 4, 10       |

Groups 1a and 1b are sized for safety rather than immunogenicity, as the higher dose is expected to be necessary for an adequate immune response. Participants in Group 2 will receive 4 doses of vaccine to allow estimation of the effect of the additional dose of vaccine on immunogenicity. A fourth dose was added to explore if a booster dose will increase antibody responses, as preliminary results suggest that antibody responses increase with each of the first 3 doses. In addition, subjects of Group 1a and Group 1b who were exceptionally high (>500 EU) anti-Pfs25 antibody producers as measured by ELISA assay after the second dose will be offered the opportunity to receive a booster dose at 10-11 months. The purpose of this is to obtain high-titer antibodies and evaluate whether transmission blocking activity correlates with the antibody titers. Table 2 shows the vaccination and dose escalation schedule for the 2 groups; first vaccinations within dose groups are staggered for assessment of safety of the vaccine in a small number of subjects in each dose group prior to further enrollments.

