**Group 2 subjects who do not receive optional booster dose****Study Day 480 ±14 Days**

1. Perform directed history and assessment of any physical complaint.
2. Record vital signs.
3. Obtain blood for anti-Pfs25 ELISA, and T and B cell studies.

**Group 2 and select high-responders in Group 1****Study Day 300 ±14 Days (Day of Third or Fourth Vaccination-approximately 6 months since third vaccination for Group 2, up to 9 months after second vaccination for Group 1)**

1. Perform basic history and focused physical examination, emphasizing examination of any acute complaints.
2. Review criteria for vaccination.
3. Obtain blood for CBC with differential and platelet count, ALT, creatinine, anti-Pfs25 antibody ELISA, and B and T cell studies.
4. For females, obtain a urine or serum sample for  $\beta$ -hCG testing. Ensure that the test is negative before vaccinating; a positive test will exclude the subject from vaccination. Review pregnancy prevention counseling.
5. Obtain a urine sample for dipstick testing and ensure that protein and blood are no more than trace positive before vaccinating. Should a female subject be menstruating on the day of vaccination, she will not be excluded from vaccination if she has more than trace blood in her urine.
6. Record vital signs (blood pressure, temperature, heart rate, and respiratory rate).
7. Administer the vaccine.
8. Observe for at least 30 minutes after vaccination to evaluate for immediate adverse reactions.
9. Review of proper use of digital thermometer, injection-site reaction measurement tool, and memory enhancement card (diary) by study staff during 30-minute post-immunization wait period. Study staff will also discuss signs and symptoms of potential AEs, and indications for use of antipyretics (acetaminophen or ibuprofen) if fever, headache, or malaise occurs.

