## 9.3 Assessment of Adverse Events

Assessment of safety will include clinical observation and monitoring of hematological, chemical, and immunologic parameters. Subjects will be closely monitored for 30 minutes following each immunization. Additionally, subjects will return to the clinic on Days 3, 7, 14, and 28 following each vaccination for clinical assessments, and periodically thereafter until completion. All AEs will be recorded through Day 28 after each vaccination. Injection site reactions will be assessed until day 14 or until resolved. After that period only SAEs, UPs, and NOCIs ([Section 9.1](#)) will be recorded.

All AEs will be graded for severity and assessed for relationship to the study product. Reactions

will be graded as described in this protocol. A study clinician will be available 24 hours a day during the study period. Should a subject call a study clinician to report an AE, it will be fully documented in the subject's study chart, and discussed with the PI.

All local and systemic reactions will be captured on the appropriate source documents and CRIMSON Data System. Those assessed as serious will be further reported on the Sponsor's SAE/UP report form. AEs judged to be possibly, probably, or definitely related to the study product will be followed to adequate resolution. All concomitant medications will be collected through day 28 after each vaccination; new chronic medications will be collected for the remainder of the study.

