To test for an antibody response by dose between the three dose groups, we use the Jonckheere-Terpstra (J-T) test which is a generalization of the Wilcoxon Mann Whitney (WMW) test from two groups to three or more ordered groups (e.g., low, middle and high dose groups). For the sample size calculations, we consider the simpler situation where the lower two dose groups are combined into one group and tested by WMW test. This simpler situation ignores differences in antibody response between the two lower dose groups; therefore the actual J-T test which does not ignore those differences should be at least as powerful as the simplifying situation. For the power calculation for the simplified situation we first estimate the standard deviation of the (log transformed) antibody response. To do this, we use data on the 5 subjects who received 2 doses of Pfs25/ISA51 vaccine in [Wu et al 2008]. From that data the standard deviation of the log transformed ELISA responses 2 weeks after the second vaccination was 0.33. After accounting for the fact that the standard deviation was estimated from only 5 observations [Fay et al 2007], a Z-test of the difference in means with 4 and 16 observations would have about 80% power to reject at the 2-sided 0.05 level if the geometric mean ELISA values was 4.5 fold higher in the larger dose group (the group with n=16). Because we use the WMW test instead of a Z-test, these results should hold with an increase in the sample size by 5% since the WMW test is about 95.5% as efficient as a Z-test in this situation [Lehmann 1999], i.e., the sample sizes of 10 (low and middle dose combined) and 20 (high dose) will have about 80% power to show a 3 fold difference between the lower two doses and the high dose. Thus, when we use the information

about differences between the low and middle dose groups (i.e., use the J-T test), we should have at least 80% power if there was a difference of 3 fold between the middle and high dose and possibly a larger difference between the low dose and high dose.

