### **11.5 Randomization**

Randomization for Group 2 will be done in blocks by the study site pharmacist. Subjects and investigators will be aware of Group assignment. (Note: subjects in Group 2 were initially randomized into Group 2a (0, 2 month schedule) and Group 2b (0, 2, 4 month schedule), but these groups were subsequently collapsed into Group 2 (0, 2, 4 month schedule.) A fourth dose was later added for Group 2 and selected high responders in Group 1 at 10 months.

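### Section 11.2.d tests the proportion with at least 1 AE across groups planned for 2 versus 4 doses without fixing a common exposure window, so the contrast cannot be read as a dose effect

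*Protocol*

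**What the plan says.** Item d of Section 11.2 sets the endpoint and the contrast: "The proportion of subjects with at least 1 AE will be compared by vaccine schedule and/or dose group". It then calls for "tests performed to assess whether these groups differ with respect to these proportions". It names neither the test nor the period over which AEs are counted.

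The dosing is unequal by design. The Précis states: "The low dose groups will receive 2 doses of vaccine and the high dose group will receive 4 doses of vaccine". Section 3.1 adds that high responders in Groups 1a and 1b "will be offered the opportunity to receive a booster dose at 10-11 months". Section 6.4 and Appendix B carry a separate schedule for "Group 2 subjects who do not receive optional booster dose", so some Group 2 subjects may stop before the fourth dose.

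AE collection follows the doses. Section 9.3 says: "All AEs will be recorded through Day 28 after each vaccination". After that, only SAEs, unanticipated problems and new chronic illnesses are recorded.

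Group 2 was at first randomised between a 2-dose and a 3-dose schedule. Section 11.5 records that "these groups were subsequently collapsed into Group 2" on the 3-dose schedule, with a fourth dose added later.

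**The concern.** A proportion with at least one event can only rise as doses, observation days and laboratory draws accumulate. Section 11.2.d compares such a proportion between groups whose planned exposure differs by a factor of two, and it offers the comparison by dose group. An apparent excess at 47 µg could then come from the number of injections alone, and a reader of the result could not tell.

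The wording also treats schedule and dose as alternative groupings. With Groups 2a and 2b merged, no planned 2-dose arm remains at 47 µg, and no 4-dose arm exists at 8 or 16 µg. As planned, the two groupings are nearly the same split.

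Safety and reactogenicity are the primary objective, and Section 11.4 links the safety data to proceeding to a study in a malaria-exposed population. Section 11.3 avoids the problem for antibody, because it fixes the dose comparison at 2 weeks after the second vaccination in all three groups.

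**Working it through.** **Inputs from the protocol.**
- Group sizes are 5 + 5 = 10 at the two lower doses and 20 at 47 µg (Table 1; Section 11.4 uses the same pooling for the antibody calculation).
- Planned doses are 2 and 4 (Précis, Table 1).
- All-AE collection lasts 28 days per dose: 2 × 28 = 56 days, 3 × 28 = 84 days, 4 × 28 = 112 days (Section 9.3).
- Laboratory values are solicited AEs (Table 3). Post-dose CBCs in Section 6.4 fall on Days 3, 7, 14, 59, 63 and 70 for Group 1, which is 6. A fully dosed Group 2 subject adds Days 123, 127, 134, 303 and 314, which makes 11.

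**Assumptions.** The documents give no per-dose AE risk q, so a range is shown. Fisher's exact test, the pooled 10 vs 20 split and two-sided 0.05 are also assumed. The protocol states that level only for the antibody power calculation.

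**The plan's own safety figures.** Section 11.4 uses 1 − (1 − p)^n and claims a probability of about 0.80. For n = 5, p = 0.275: 1 − 0.725^5 = 0.7997. For n = 30, p = 0.052: 1 − 0.948^30 = 0.7985. Both reproduce. No figure is given for the between-group AE test.

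**Same per-dose risk in every group.** With independent doses, P(at least 1 AE over k doses) = 1 − (1 − q)^k. For q = 0.3 this is 1 − 0.7² = 0.510 for 2 doses and 1 − 0.7⁴ = 0.760 for 4. The rejection probability comes from enumerating every outcome of Binomial(10) × Binomial(20).

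| q | 2 doses | 4 doses | Fisher rejects |
|---|---|---|---|
| 0.05 | 9.8% | 18.5% | 1.0% |
| 0.1 | 19.0% | 34.4% | 7.9% |
| 0.2 | 36.0% | 59.0% | 14.1% |
| 0.3 | 51.0% | 76.0% | 23.5% |
| 0.4 | 64.0% | 87.0% | 25.7% |
| 0.5 | 75.0% | 93.8% | 23.3% |
| 0.6 | 84.0% | 97.4% | 14.3% |
| 0.7 | 91.0% | 99.2% | 4.7% |
| 0.8 | 96.0% | 99.8% | 0.6% |

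The gap peaks at 25 points, near q = 0.29.

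**Variations at q = 0.3.**
- Group 2 stops at 3 doses: 51.0% vs 1 − 0.7³ = 65.7%; rejection 8.6%.
- Half of Group 1 boosted: (5 × 0.510 + 5 × 0.657)/10 = 58.4% vs 76.0%; rejection 13.6%.
- Within-subject correlation ρ, beta-binomial with a = q(1/ρ − 1) and b = (1 − q)(1/ρ − 1): ρ = 0.3 gives 44.7% vs 59.7%, rejection 7.5%. ρ = 0.5 gives 40.5% vs 50.5%, rejection 4.5%.

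**Common exposure.** If only the first two doses count in every group, equal per-dose risk gives equal expected proportions. Fisher's test then rejects in about 3% of trials at most (2.6% at q = 0.3).

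**The case against.** The strongest reply is that Section 11.2.d states no counting window. Windows and test choice are often left to an analysis plan, and item d goes on to a per-vaccination analysis. Counting over all doses is indeed the natural reading rather than a stated rule. But the protocol itself fixes the endpoint, the groups and the fact of testing. The per-vaccination Wilcoxon test is within subject and does nothing for the between-group contrast.

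Four stronger readings are tempting, and the documents do not support them.

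- *This is the trial's primary safety comparison.* The protocol does not call it that. It is one of five analyses (a to e) in a study that Section 11.1 calls exploratory, although that section keeps formal tests. Halting (Section 9.5) rests on event counts, and no decision is tied to this p-value.
- *Dose and number of doses are completely confounded in every subject.* Section 6.2 allows a Group 2 booster after at least 2 previous doses, Section 6.4 provides for Group 2 subjects without it, and some Group 1 subjects may get a third dose. The planned schedules coincide with dose level; actual exposure will be mixed.
- *The test will usually show a false difference.* The bias is in expectation. Even in the worst case tabulated, about 74% of trials show no significant difference. AEs are defined broadly, so high per-dose risks are plausible, and at 70% or more rejection is under 5%.
- *The schedule comparison must be removed.* The burden of a full 2-dose versus a full 4-dose regimen is a legitimate quantity. It lacks a label.

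That the comparison survives from the time when Group 2 was randomised between schedules is plausible, but no text shown establishes it.

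**Conclusion.** The point holds in a limited form. Read as written, Section 11.2.d compares a cumulative proportion across unequal planned exposure, is biased towards more AEs at 47 µg, and cannot be interpreted as a dose effect. Under equal, independent per-dose risks of 20% to 40%, the spurious gap is 23 to 25 points, with rejection in 14% to 26% of trials. That range lies near the peak of the bias. Correlation between doses in the same person, incomplete dosing in Group 2, boosters in Group 1, and very low or very high risk all reduce it, in several cases to below the nominal 5%. The direction of the bias rests on the text alone; its size depends on a per-dose risk that the documents do not give. The comparison of Group 1a with 1b is unaffected unless the optional boosters fall unevenly between them.

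**What to change.** In Section 11.2.d, base the between-dose-group comparison on AEs from Day 0 through 28 days after the second vaccination, censored at any third dose. Censoring is needed because the stated windows can overlap: a second dose on Day 56 + 14 = 70 runs to Day 98, and a third dose may fall on Day 120 − 28 = 92. Report the same comparison separately for dose 1 and dose 2.

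Summarise AEs after later doses per dose within group: doses 3 and 4 in Group 2, and the optional booster in Group 1. If an all-doses comparison is kept, label it as a whole-regimen comparison in which dose level and number of doses cannot be separated.

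The cost is one paragraph and no new data. AEs after doses 3 and 4 leave the between-group dose test but are still reported.
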